## Abstract

**Introduction:** Unexplained heterogeneity in outcomes following pediatric traumatic brain injury (TBI) is one of the most critical barriers to the development of effective prognostic tools and therapeutics. The addition of personal biological factors to our prediction models may account for a significant portion of unexplained variance and advance the field toward precision rehabilitation medicine. The overarching goal of the Epigenetic Effects on Pediatric Traumatic Brain Injury Recovery (EETR) study is to investigate an epigenetic biomarker involved in both childhood adversity and postinjury neuroplasticity to better understand heterogeneity in neurobehavioral outcomes following pediatric TBI. Our primary hypothesis is that childhood adversity will be associated with worse neurobehavioral recovery in part through an epigenetically mediated reduction in brain-derived neurotrophic factor (*BDNF*) expression in response to TBI.

**Methods and analysis:** EETR is an observational, prospective, longitudinal concurrent cohort study of children aged 3–18 years with either TBI (*n* = 200) or orthopedic injury (*n* = 100), recruited from the UPMC Children's Hospital of Pittsburgh. Participants complete study visits acutely and at 6 and 12 months postinjury. Blood and saliva biosamples are collected at all time points—and cerebrospinal fluid (CSF) when available acutely—for epigenetic and proteomic analysis of *BDNF*. Additional measures assess injury characteristics, pre- and postinjury child neurobehavioral functioning, childhood adversity, and potential covariates/confounders. Recruitment began in July 2017 and will occur for ~6 years, with data collection complete by mid-2023. Analyses will characterize *BDNF* DNA methylation and protein levels over the recovery period and investigate this novel biomarker as a potential biological mechanism underlying the known association between childhood adversity and worse neurobehavioral outcomes following pediatric TBI.

**Ethics and dissemination:** The study received ethics approval from the University of Pittsburgh Institutional Review Board. Participants and their parents provide informed consent/assent. Research findings will be disseminated via local and international conference presentations and manuscripts submitted to peer-reviewed journals.

**Trial Registration:** The study is registered with clinicaltrials.org (ClinicalTrials.gov Identifier: NCT04186429).

## Introduction

Traumatic brain injury (TBI) is a leading cause of morbidity and mortality in childhood (1). The scientific evidence available to guide prognosis, management, and treatment is disproportionately low relative to TBI's medical and societal burden. Children sustaining moderate to severe TBI often demonstrate neurobehavioral impairments that hamper their long-term functioning (2–4). Previous large-scale cohort studies in pediatric TBI have identified injury (e.g., severity, neuropathological, accidental vs. nonaccidental), developmental (e.g., age at injury, time since injury), child (e.g., premorbid functioning), and psychosocial (e.g., socioeconomic status, family functioning) factors as significant determinants of outcomes (5–12). Current prediction models including these factors, however, explain only ~35% of variance in outcomes (13). Without the identification of additional factors influencing recovery, this unexplained heterogeneity will remain one of the most critical barriers to accurate prognostication and to the development of evidence-based treatments for the neurobehavioral consequences of pediatric TBI (14, 15).

The addition of personal biological factors or “biomarkers” in our prediction models may account for a significant portion of unexplained variance. This would advance the field of pediatric TBI toward precision rehabilitation medicine, to thereby improve individual prognostication, predict response to rehabilitation, and identify novel targets for therapy development. A biomarker gaining traction in TBI research is genetic variation, with the hypothesis being that certain individuals may be genetically predisposed to worse recovery and outcomes (16–18). The investigation of genetics without consideration of factors that modulate gene expression, however, precludes a more integrative and comprehensive understanding of the biological and environmental mechanisms affecting recovery.

Over the last decade, the field of epigenetics has become central to studying the modulation of genetic phenotypes by environmental factors. Broadly defined, epigenetics involves biochemical processes that regulate gene expression without altering the corresponding primary DNA sequence (19). Through epigenetic processes, the social and biological environment of an individual impacts when and to what extent genes are expressed within each cell type. The best-characterized epigenetic mechanism is DNA methylation, with higher levels rendering the gene less transcriptionally active (20).

Among the strongest epigenetic influences on child development is the family environment, especially when it involves exposure to childhood adversity (21, 22). Children who experience greater adversity, such as poverty, separation from a parent, and maltreatment, show altered methylation profiles in genes involved in the function of the hypothalamic–pituitary–adrenal axis, immune response, and neuronal development and neuroplasticity (21, 23, 24). In turn, these altered methylation profiles are associated with higher prevalence of chronic health conditions (25), as well as a multitude of neurobehavioral phenotypes, including depression and anxiety, borderline personality disorder, attention problems, and poor impulse control (23, 24, 26–28).

In pediatric TBI, decades of research demonstrate worse outcomes in children exposed to greater adversity, including lower socioeconomic status, greater family dysfunction, and abusive head trauma as the injury mechanism (4, 5, 10, 29, 30). Despite these established findings, the biological mechanisms underlying these effects are unknown. Given the known influence of childhood adversity on both children's epigenetic profiles and recovery from pediatric TBI, the effect of childhood adversity on recovery may be mediated by epigenetic mechanisms.

The brain-derived neurotrophic factor (*BDNF*) gene is an ideal candidate for the first exploratory examination of epigenetic influences on neurobehavioral recovery following pediatric TBI because it is involved in both: (1) the biological response to childhood adversity and (2) neuroplasticity following TBI. BDNF is a well-studied member of the neurotrophin family of growth factors. It is released from neurons both pre- and postsynaptically and mediates apoptosis, neuronal differentiation, outgrowth of neurites, cell survival, and synaptic strengthening (31, 32). Thus, BDNF is intimately involved in brain development, neuroplasticity, and neuronal survival (33, 34), as well as complex cognitive processes, including learning/memory (35, 36) and executive functioning (37–40). A single-nucleotide polymorphism producing a valine-to-methionine substitution at codon 66 (val66met) in the *BDNF* gene is associated with reduced activity-dependent secretion of BDNF (41) and may modify methylation level at this position on the gene (42–44). In addition to other transcriptional and translational regulators (45, 46), *BDNF* gene expression, as is the case with many genes, is regulated in part by DNA methylation, such that higher methylation is associated with lower neuronal synthesis of BDNF (47).

*BDNF* DNA methylation epigenetically encodes the effects of childhood adversity on neurodevelopment. Multiple recent studies show that early adversity produces changes in *BDNF* methylation detectable in the brain and peripheral biosamples in both animal models (48–50) and humans (23, 51–53). Both higher *BDNF* methylation (23, 54) and lower BDNF protein levels (55–60) are associated with worse neurobehavioral outcomes in children with preterm birth, attention-deficit/hyperactivity disorder (ADHD), bipolar disorder, anorexia, and autism spectrum disorder.

The BDNF pathway is also involved in neural recovery from TBI. BDNF is upregulated in the frontal cortex and the hippocampus after experimental TBI and may mediate recovery processes after brain injury (61–63). In adult clinical studies, BDNF levels in cerebrospinal fluid (CSF) show a sharp spike within 24 h postinjury and steadily decline over 1 week (64, 65), providing evidence for BDNF upregulation and involvement in recovery post-TBI consistent with animal models. BDNF levels during the first week postinjury tend to be comparable in CSF (65) but lower in serum in adults with TBI relative to nonbrain-injured controls (65, 66). Furthermore, acute and chronic BDNF levels in CSF and serum/plasma after TBI in adults predict outcomes, including mortality (65), global outcomes (66, 67), and long-term functional cognition and depression (68, 69). Far fewer studies have examined BDNF levels after pediatric TBI. Initial evidence shows a sharp peak in BDNF levels immediately following injury, followed by subsequent declines (70, 71), similar to that shown in adults. Higher CSF and plasma/serum BDNF levels predicted better global recovery in pediatric TBI studies (71, 72), but to our knowledge, no known studies have examined *BDNF* genetics or epigenetics in association with TBI outcomes in children.

Thus, the overarching goal of our study is to investigate an epigenetic biomarker involved in both childhood adversity and postinjury neuroplasticity to better understand heterogeneity in neurobehavioral outcomes following TBI. Our primary hypothesis is that childhood adversity will be associated with worse neurobehavioral recovery in part through an epigenetically mediated reduction in *BDNF* expression in response to TBI (see Figure 1).

**Figure 1 F1:**
[figure not shown]
Heuristic model of our primary hypothesis. **(A)** Children with greater childhood adversity may have higher pre-TBI *BDNF* methylation, which may lead to **(B)** higher *BDNF* methylation and lower BDNF protein levels in response to TBI and over the recovery period, resulting in lower neuroplasticity and worse neurobehavioral outcomes. **(C)** This pathway may contribute to a biological explanation for the association between greater childhood adversity and worse neurobehavioral outcomes following pediatric TBI. BDNF, brain-derived neurotrophic factor; OI, orthopedic injury; TBI, traumatic brain injury.

The study uses an observational, prospective, longitudinal concurrent cohort design to examine the epigenetic influence of the biologically relevant *BDNF* pathway on neurobehavioral recovery in 200 children with nonpenetrating complicated mild to severe TBI relative to 100 children with orthopedic injury (OI) but no brain injury at three time points (acute, 6 months, 12 months) during the first year of recovery. As one of the first studies of epigenetic effects in pediatric TBI, this is an exploratory pilot study. The study will establish a longitudinal biorepository that is innovative in its integration of acute and chronic biological samples with comprehensive data characterizing preinjury childhood adversity and postinjury neurobehavioral functioning. Only a portion of each biosample will be used for the analyses proposed in the present study; the remaining biosamples will be stored in the biorepository. This rich biorepository will be expanded longitudinally in subsequent studies and will provide opportunities to evaluate other epigenetic, genetic, and protein biomarkers and biological mechanisms in future secondary analyses. The results of the present pilot study will guide the design of a subsequent larger multisite study that will be sufficiently powered to examine additional epigenetic biomarkers while controlling for additional sources of heterogeneity in outcomes.

Our specific aims and hypotheses are as follows:

Aim 1: Examine differences between TBI and OI in *BDNF* methylation and BDNF protein levels over the recovery period. We hypothesize that *BDNF* methylation will be higher, and BDNF protein levels will be lower, in children with TBI relative to OI at all time points, and that *BDNF* methylation will decrease, and BDNF protein levels will increase, in the TBI group over time but will remain relatively stable in the OI group.Aim 2: Characterize trajectory classes of *BDNF* methylation and BDNF protein levels following TBI while controlling for potential demographic, injury, and lifestyle covariates. We hypothesize the presence of at least two *BDNF* methylation trajectory classes and two BDNF protein level trajectory classes representing varying degrees of recovery from TBI. We will explore age, sex, pubertal status, TBI severity, overall injury severity, body mass index (BMI), and smoking as potential covariates.Aim 3: Test the indirect effect of childhood adversity on neurobehavioral recovery following pediatric TBI, as mediated by *BDNF* methylation and BDNF protein level trajectory classes.

## Methods and Analysis

### Study Overview

Children aged 3–18 years with either complicated mild to severe nonpenetrating TBI (*n* = 200) or OI (*n* = 100) are recruited from consecutive overnight admissions to the UPMC Children's Hospital of Pittsburgh (CHP). The sample size of 200 children with TBI and 100 children with OI was chosen based on two considerations: (1) feasibility of recruitment over the study period based on historic numbers of children with TBI meeting eligibility criteria at our site and (2) adequacy of statistical power for proposed analyses taking into consideration participant attrition over the study period (see section Statistical Methods and Power). We selected the age and severity ranges to optimize sample size for this initial exploratory pilot study and to examine the effects of demographic and injury factors as potential covariates to inform design of future studies. In addition, most neurobehavioral measures selected for use in the study have age-specific forms spanning this age range. To ensure an adequate distribution across TBI severity and because disproportionately more children sustain complicated mild relative to moderate to severe TBI, we will stratify TBI recruitment into two severity groups (complicated mild vs. moderate/severe) and recruit consecutively within each group until we have at least 20% of the total sample in the moderate to severe TBI group. Children with OI were selected as a comparison group to control for premorbid risk factors for injury of any kind and to equate for the experience of having a traumatic injury and associated medical treatment (73, 74). In addition, comparing biomarkers between traumatically injured children with and without injury to the brain will help differentiate general injury effects on systemic biomarkers from those that are specific to brain injury (75). Children with spinal cord injury are excluded from both the TBI and OI groups to avoid confounding from neuroinflammation and brain involvement.

Data are collected at three time points postinjury. Acute data collection occurs before hospital discharge, and chronic data collection occurs at 6 and 12 months postinjury during outpatient follow-up visits to CHP. Data are collected pertaining to hypothesized predictors of neurobehavioral recovery (e.g., demographics, injury information, child premorbid functioning, childhood adversity, and biomarkers), neurobehavioral outcomes (e.g., neuropsychological test performance, parent-rated neuropsychological, emotional/behavioral, and adaptive functioning), and potential covariates/confounders (e.g., BMI, pubertal status, tobacco/nicotine exposure, bodily injury severity). Recruitment began in July 2017 and will occur for ~6 years, with data collection complete by mid-2023.

DNA methylation patterns are tissue specific and reflect the local environment of each cell type, and examination of brain tissue is not feasible in patients who survive their injuries; therefore, determining which types of biosamples serve as effective proxies for the CNS environment is an important methodological consideration. Moreover, to be useful as a clinical biomarker, markers must be found in readily accessible biosamples, such as blood or saliva. Several previous studies have shown that methylation in peripheral biosamples, including blood and saliva, is strongly correlated with methylation in brain tissue or CSF (46, 76–81) for several target genes, including *BDNF* (46, 77). Methylation measured in peripheral biosamples may be of even greater prognostic value in TBI compared to neuropsychiatric conditions because brain-specific biomarkers may enter blood circulation in TBI not only through disruption to the blood–brain barrier but also through the glymphatic system (82). Finally, a recent review of the “tissue issue” concluded that the limitations of examining epigenetic brain biomarkers in peripheral tissues or biosamples are surmountable and discussed methodological advantages of using peripheral biosamples: serial biosampling, longitudinal study designs and related causal modeling options, large participant sample sizes yielding statistical power to detect modest effects, and translational utility in clinical settings (83).

In light of these methodological considerations, we collect saliva and blood biosamples at acute and chronic time points in all participants. We also collect acute serial CSF samples in the small subsample of participants with extraventricular drain (EVD) placement to manage intracranial pressure as part of guidelines based standard of care (84).

### Inclusion Criteria

Children in both groups must be from 3 to 18 years of age at the time of the injury. Children with TBI must be hospitalized overnight for a complicated mild to severe nonpenetrating TBI as defined by the lowest postresuscitation Glasgow Coma Scale (GCS) score (85). Complicated mild TBI is defined as a GCS of 13–15 with neuroimaging indicating intracranial or parenchymal injury or depressed/displaced skull fracture. Moderate TBI is defined as GCS of 9–12. Severe TBI is defined as GCS of 3–8. Children are included in the OI group if they sustain a bone fracture, excluding to the skull or face, without any signs of head trauma or brain injury (e.g., nausea/vomiting, headache, loss of consciousness, GCS below 15 at any point).

### Exclusion Criteria

Children in both the TBI and OI groups meet the following exclusion criteria: (a) non-English-speaking child or non-English-speaking parents/guardians; (b) documented or parent-reported history of previous TBI/concussion requiring overnight hospitalization; (c) preinjury neurological disorder or intellectual disability; (d) preinjury psychiatric disorder requiring hospitalization; (e) spinal cord injury; (f) sensory or motor impairment precluding study measure completion; and (g) pregnancy at the time of study participation. Participants are also excluded if at least one biosample is not able to be collected within 7 days of the injury. Children in the TBI group are not excluded if they also have an OI.

### Study Procedures

The study staff screen the CHP electronic medical record (EMR) daily to identify children who are potentially eligible for study participation. Children are housed in one of two settings when they are identified: (1) the acute care trauma unit or (2) the pediatric intensive care unit (PICU). Children housed in the acute care trauma unit within the first week of their injury are approached about the study. The study staff approach families and conduct brief interviews about the child's preinjury functioning and medical history to confirm eligibility and obtain informed consent prior to any data collection. Interested parent(s) of minor children, and 18-year-old patients capable of consenting on their own behalf, provide written informed consent. Children over the age of 8 capable of understanding study procedures provide assent.

Children with more severe injuries are sometimes housed in the PICU during the acute biosample window (i.e., 1 week postinjury). If a potentially eligible child is in the PICU, the bedside nurse collects the acute blood sample at the same time as a clinical blood draw, before consent has been obtained per an Institutional Review Board (IRB)-approved waiver of informed consent. In addition, if a child with severe TBI has an EVD placed as part of routine clinical care, the bedside nurse collects daily CSF samples up to 1 week postinjury prior to study consent. Families of children whose samples are collected preconsent are approached about study participation once the child is medically stable, usually after discharge to the acute care trauma unit. If the family declines to participate or the child is discovered through screening questions to be ineligible, the preconsent samples are destroyed. Destruction of preconsent samples is requested by the research coordinator and completed by research nurses in the CHP Pediatric Clinical and Translational Research Center (PCTRC). Documentation of sample destruction is maintained both by the PCTRC and by the research coordinator.

For children and families who consent to study participation, an additional postconsent blood sample is obtained by the bedside nurse in addition to any preconsent acute blood and CSF samples. The study staff collect a saliva sample from the child. Prior to discharge, parents complete measures pertaining to demographic information, premorbid child functioning, childhood adversity, child resilience, and the child's pre- and postnatal exposure to nicotine/tobacco. Children 8 years and older complete a self-report measure of puberty status, and children 10 years and older also complete a self-report measure of tobacco/nicotine use. Injury information (e.g., mechanism, neuroimaging results, GCS) and BMI are obtained from the child's EMR.

The study staff contact families to schedule their 6- and 12-month follow-up research visits at CHP. Follow-up visits last ~90 min. At each visit, PCTRC research nurses collect blood via venipuncture, and the study staff collect saliva. Parents complete the same measures as the acute visit, this time to assess postinjury functioning (see Table 1 and Section Measures). Children complete the National Institutes of Health Toolbox-Cognition Battery (NIHTB-CB) and self-report measures of puberty and tobacco/nicotine use. Families who refuse to return for follow-up research visits are given the option to return parent study measures and the child saliva sample via mail. Families are provided with instructions for how to collect the saliva sample and complete the parent measures as well as return packaging and postage.

**Table 1 T1:** Study measures organized by domain, source of data, and assessment occasion.

**Domain/measures**	**Source/reporter**	**Parent/child time to complete (min)**	**Acute (preconsent)**	**Acute (postconsent)**	**6 months**	**12 months**

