### Outcomes

Child neuropsychological function is assessed acutely and at each follow-up visit using the NIHTB-CB (97). The NIHTB-CB is a 30-min battery of standardized neuropsychological tests administered on an iPad. The NIHTB-CB provides norm-referenced scores for the domains of language, episodic memory, processing speed, working memory, and executive function, as well as an overall cognitive function composite score.

Parent-reported child postinjury executive, emotional/ behavioral, and adaptive functioning are measured at follow-up visits using the BRIEF-2/P, SDQ, Vineland-3, and resilience items from the CHIP. Postinjury adversity is measured using the PAT and child resilience by the CHIP.

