### Data Reduction, Missing Data, and Attrition

Measures were selected that provide composites or summary indices representing each construct, reducing the need for substantial data reduction. Children will be eligible to remain in the study if at least one acute biosample (CSF, blood, or saliva) is obtained and both primary parent questionnaires (BRIEF-2/P, SDQ) are completed. This will reduce missing data on key variables and retain participants who refuse blood collection or are unable to produce sufficient saliva. In addition, statistical techniques such as mixed models, latent class trajectory analysis, and path analysis will be used, which estimate models based on all available data using maximum likelihood estimation (108). Consistent with previous studies in this population, we conservatively estimate that ~75% of participants will complete the follow-up visits (150 TBI; 75 OI) (2, 4, 5). Our power analyses account for this reduced participant sample size at follow-up.

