### Data Analyses

#### Biomarker Analysis

DNA extracted from saliva, blood, and CSF will be processed for methylation analysis. We currently plan to use EpiTect Methyl II PCR assays (Qiagen, Germantown, MD) to assess targeted methylation sites in and around the *BDNF* gene; however, due to rapid changes in technology for this type of data collection, when data collection is to begin, we will evaluate whether this method remains our best choice. We will target a select number of *BDNF* CpG islands for this initial study that showed the strongest correlation between blood and CSF in our preliminary data (109) and show significant correlations between *BDNF* methylation in blood and postmortem prefrontal cortex brain tissue according to the searchable online Blood Brain DNA Methylation Comparison Tool (110). Additional *BDNF* methylation targets may be examined in secondary analyses. The resulting data will estimate the methylation level at each CpG site by beta values (i.e., percent methylation). Beta values range from zero to 1, with zero indicating a null methylated site and 1 indicating a fully methylated site. *M* values will then be calculated and used in statistical analysis. (111, 112) Plasma BDNF protein levels will be measured using an ELISA kit according to the manufacturer's instructions. BDNF ELISA kits are available from several manufacturers (e.g., RayBiotech, R&D Systems). We will select a manufacturer at the time of analysis based on available specifications. For quality control, biosamples will be batch analyzed, assays will include biological duplicates and technical replicates, and data will be evaluated by two individuals blinded to phenotype.

Before our main analyses, we will examine the concordance of *BDNF* methylation across saliva, blood, and CSF and compare the predictive value of epigenetic results across biosample types. Based on these results, we may determine that saliva or blood biosamples are more informative than the other, and these results will guide which biosample(s) are used for measurement of *BDNF* methylation in our primary analyses.

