##### Aim 3: Test the indirect effect of childhood adversity on neurobehavioral recovery following pediatric TBI, as mediated by BDNF methylation and BDNF protein level trajectory classes

We will conduct path analysis to test the theoretical model shown in Figure 2 within the TBI group. The theoretical model represents the relation among constructs rather than specific measures to allow for fluidity in our approach. For example, we will examine this model for each of the four primary measures of neurobehavioral outcome (NIHTB-CB, BRIEF-2/P, SDQ, Vineland-3). The specific biosamples used for *BDNF* methylation will be informed by preliminary analyses (see *Biomarker Analysis*). Path analysis enables a graphical representation of complex relationships, can explore direct and indirect effects among the variables (e.g., mediation), and infer causal directionality between effects. *BDNF* methylation and protein level trajectory class adjusted for covariates (Aim 2) will be tested as categorical mediators. Neurobehavioral recovery on each outcome will be modeled controlling for premorbid functioning (with the exception of NIHTB-CB). We estimated sample size requirements to adequately power the three single mediator models that would comprise our double-mediator model, as current guidelines on sample size for double mediator models are limited. The power of a single mediator model depends on the effect of the independent variable (IV) on the mediator and the effect of the mediator on the DV, controlling for the IV. Using Cohen's effect size criteria, we expect to have sufficient power (≥0.8) if both effects are at least “halfway” (between small and medium effects) (121). However, we would only need 115 participants if one effect is “halfway” and the other is medium. Thus, our final sample is conservative.

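### Mailed parent ratings could inform the missing NIHTB-CB scores of children who do not attend, but the separate NIHTB-CB path model, as described, does not use them (minor, near-free improvement)

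*Protocol article*

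**What the plan says.** Under Study Procedures, follow-up blood is tied to attendance: "At each visit, PCTRC research nurses collect blood via venipuncture". Families who refuse to come back are "given the option to return parent study measures and the child saliva sample via mail". Under Outcomes, the NIHTB-CB is a set of "standardized neuropsychological tests administered on an iPad", so it is not part of the mail packet. Under Biomarker Analysis, "Plasma BDNF protein levels will be measured using an ELISA kit", and mailed saliva cannot supply plasma.

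For Aim 3 the article states that "we will examine this model for each of the four primary measures of neurobehavioral outcome". Each outcome is adjusted for premorbid functioning except the NIHTB-CB. Missing data are addressed under Data Reduction, Missing Data, and Attrition by naming mixed models, latent class trajectory analysis and path analysis, "which estimate models based on all available data using maximum likelihood estimation". The same section expects about 75% of participants to complete the follow-up visits (150 TBI, 75 OI).

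**The concern.** The design creates a group of children who have a same-visit measure of functioning but no NIHTB-CB score. Maximum likelihood handles the missing scores correctly if return depends only on variables in the fitted model. The NIHTB-CB model contains adversity, BDNF classes and covariates. It is the one model of the four with no earlier measure of the child's functioning, and nothing says that the parent ratings enter it. If families of poorly functioning children return less often at a given level of adversity, the observed NIHTB-CB scores are selected in a way this model cannot see, although data that could reveal it have been collected.

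At stake is the split between direct and indirect effects on the NIHTB-CB, and whether a difference between NIHTB-CB and parent-rated findings partly reflects which children attended.

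**Working it through.** **The plan's own figure.** 0.75 × 200 = 150 TBI and 0.75 × 100 = 75 OI, as stated. The check therefore takes 1 − 0.75 = 25% as the share without a follow-up NIHTB-CB.

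**What a mail-in child supplies at that visit**

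| Item | Attends | Mails | Sends nothing |
|---|---|---|---|
| BRIEF-2/P, SDQ, Vineland-3 | yes | yes | no |
| Saliva (methylation) | yes | yes | no |
| NIHTB-CB | yes | no | no |
| Plasma (protein) | yes | no | no |

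**Set-up (assumptions; the article gives no path sizes, correlations or return model).** Let x be adversity, m the mediator, y the NIHTB-CB scored so that higher is worse, and R the parent rating, all with unit variance. The planned mediators are categorical; a continuous m is a simplification.

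- m = 0.26x + error
- y = 0.26m + c′x + error, with c′ = 0.26 or 0.10
- R = r·y + error, with r = 0.3 or 0.5
- logit P(y missing) = constant + g·x + g·R, with g = 0.5 or 1.0, and the constant set to give 25% missing

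When only y is missing and R is outside the model, the likelihood for y given m and x comes from attenders alone. The estimates are then those of a regression in attenders. With 2 million draws, the estimates as a ratio to the true value are:

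| r | g | Direct effect, c′ = 0.26 | Mediator path, c′ = 0.26 | Direct effect, c′ = 0.10 | Mediator path, c′ = 0.10 |
|---|---|---|---|---|---|
| 0.3 | 0.5 | 0.958 | 0.994 | 0.880 | 0.995 |
| 0.3 | 1.0 | 0.888 | 0.990 | 0.695 | 0.989 |
| 0.5 | 0.5 | 0.928 | 0.990 | 0.808 | 0.988 |
| 0.5 | 1.0 | 0.810 | 0.977 | 0.491 | 0.973 |

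For c′ = 0.26 the direct effect is understated by 1 − 0.958 ≈ 4% to 1 − 0.810 = 19%. With 15% missing, the ratios run from 0.970 to 0.862 (3% to 14%). The mediator path loses at most about 3% in any row. The ends are approximate: with unit residual variances instead of unit total variances, the harshest ratio at c′ = 0.26 is 0.795.

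**When there is no bias.** If return is random, or depends on adversity alone, or on adversity and the mediator, a separate model with true values −0.26 (mediator) and −0.10 (direct) recovers both.

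**What the auxiliary rating repairs.** Regress y on m, x and R in attenders (coefficients q), and R on m and x in everyone with R (coefficients p). The direct effect is then q_x + q_R·p_x, and the mediator path q_m + q_R·p_m. In the harshest row (c′ = 0.26, r = 0.5, g = 1.0) the direct-effect ratio depends on how many non-attenders mail ratings, taken as a random subset of them:

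| Non-attenders who mail | Direct-effect ratio |
|---|---|
| 0% | 0.81 |
| 25% | 0.89 |
| 50% | 0.94 |
| 100% | 1.00 |

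**What it does not repair.** If return depends on the NIHTB-CB score itself, the mediator path is about −0.236 against a true −0.26. With the auxiliary rating it is −0.236 to −0.242, so most of the bias stays.

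**The case against.** The article states nothing false here. It names a recognised missing-data method, and the choice of auxiliary variables is the kind of detail that a fuller analysis plan may settle. Aim 3 also says that its model shows constructs, leaving the approach flexible, so correlates are not ruled out. This stands, and it is why the point is an improvement and not an error.

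Stronger readings are tempting, but the documents do not support them:

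- **That the NIHTB-CB result is biased.** Bias needs return to depend on current functioning beyond the modelled variables. No section gives evidence on this, or says which families stop attending.
- **That the primary claim is overstated.** Aim 3 tests the indirect effect, and no proportion mediated is planned. With c′ = 0.26 the implied share is 0.0676 / 0.3276 = 20.6%, and it would appear as about 21% to 24%. It moves more if c′ is small, but it is not the tested quantity.
- **That mail-in children contribute nothing.** Adversity is measured acutely and saliva can be mailed, so they can inform the adversity-to-methylation path. A child who misses one visit may have scores from another, since "Child neuropsychological function is assessed acutely and at each follow-up visit using the NIHTB-CB". Acute plasma still feeds the protein trajectory.
- **That the 150 and 75 are inflated by mail returns.** The article counts participants who complete the visits, and offers mail to those who refuse them. The natural reading excludes mail-ins.

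**Conclusion.** The point holds as a minor, near-free improvement. The data pattern and the separate NIHTB-CB model follow from the article. As described, the mailed ratings do not inform the NIHTB-CB estimate. The NIHTB-CB direct effect is therefore at risk of attenuation: about 4% to 19% at 25% missing with a true direct effect of 0.26, and up to about half with a true value of 0.10. The mediator path moves by about 0% to 3%, so the test of the indirect effect is little affected. All of this rests on return depending on both adversity and the child's current functioning at the assumed strengths, which the documents do not test.

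**What to change.** In the NIHTB-CB path model, include the same-visit BRIEF-2/P, SDQ and Vineland-3 summary scores as auxiliary (saturated-correlate) variables under the likelihood estimation already planned. For each outcome, report in-person and mail-in completers separately, so that readers can see which children each of the four results rests on and how much the mailed ratings can repair.

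The cost is a few more model parameters and a few lines of code, using data the study already collects. The benefit is limited by how many non-attenders mail ratings, and the results should say that dependence of return on the NIHTB-CB score itself remains uncorrected.
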